### Study Procedures

After enrollment (−t_1_), an HCP will perform a home visit (t_0_) to allocate the participant to the intervention or control group, install the monitoring devices, and carefully instruct participants about the use of the eHealth platform and monitoring devices. All oral instructions will be complemented with written and digital instruction flyers to ensure that all the instructed information can be retrieved afterward. A second home visit (t_2_) is planned after the intervention period to check all devices. Moreover, an in-person semistructured interview will be held to evaluate the user experience of the interventional and investigational technology together with filling in the feasibility and acceptance questionnaires (Multimedia Appendix 1). A third, final home visit (t_e_) will be held at the end of the study after follow-up (t_3_) to retrieve all monitoring devices and evaluate this period via the evaluation questionnaires (Multimedia Appendix 1).

### Data and Statistical Analyses

Descriptive statistics will be used to examine all continuous outcome measures expressed in mean and SD for normally distributed variables and with median and IQR for nonnormal distributed variables. Univariate analyses will be performed with SPSS software (version 22.0; IBM Corp). The homogeneity of variances will be verified with the Levene test. Histogram plots and the Shapiro-Wilk test will be used to determine whether the variables are normally distributed among the groups. A *t* test (or nonparametric Mann-Whitney U test) will be used to compare the primary outcomes between eHealth care and standard care, and *P≤*.05 will be considered significant. The analysis will be performed according to the intention-to-treat principle [51], and missing data will be handled with pairwise deletion. An interim analysis will be conducted after half the participants are done with the intervention. In case the interim analysis reveals a significant increase in health care utilization in the intervention group, this study will be prematurely ended.

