### Randomization and Blinding

Patients will be randomized to either eHealth care (intervention group) or standard care (control group) during the intervention period (t_1_) by independent block randomization at the first home visit. The electronic data capture (EDC) software Castor (Castor) will allocate the participants using stratified block randomization with multiple block sizes (2, 4, and 6) into either group A or group B with an allocation ratio of 1:1 [40]. Castor randomly mixes these block sizes and hides the block size from the executor, which guarantees concealed allocation [40]. Randomization will be stratified on the number of hospital visits concerning asthma in the past 6 months (using 4 strata: 0-1 visit, 2-3 visits, 4-5 visits, or 6 or more visits), as it is known that previous exacerbations and health care utilization are risk factors for future exacerbations [2,41]. From this point, the blinding will be broken as the researchers, HCPs, and patients will need to know whether they should prepare for, provide, or receive eHealth care, respectively.

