### Sample Size

Previous data from an eHealth clinical feasibility study (N=30) using a comparable intervention within the same patient population revealed a reduction in health care utilization of 80% [34]. This data showed an average reduction in the number of outpatient consultations from 3.9 to 0.7 (SD 1.8) per patient per half year.

A power simulation was performed for a Mann-Whitney-Wilcoxon 2-sided test. The health care utilization was assumed to be Poisson distributed with means according to the clinical feasibility study. For the control group, the Poisson rate was equated to the historical data of the pilot divided by 2 to account for the study durations. The intervention group’s rate was taken to be the postdata of the feasibility study divided by 2. As the ALPACA study makes use of the intention-to-treat principle, noncompliance to the intervention was included in the simulation. The number of nonadherent participants was random in the simulation according to a binomial distribution (similar to the clinical feasibility study data, with 3 out of 33 participants). This was used to calculate the control group rate, which is a conservative estimate of no benefit from the intervention. Together with the assumption of an Alpha Type 1 error of 0.05, the sample size calculation results in 36 (18 intervention and 18 controls), with a power of 97.1% for the primary outcome and 80% for secondary follow-up effects (assuming a lasting effect of 80%). Accounting for dropouts (n=4), we would need to include 40 children.

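### The primary test ignores the factor on which randomisation is stratified, so it is conservative and loses power to the extent that prior hospital visits predict the outcome

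*Protocol article*

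**What the plan says.** Under Randomization and Blinding the protocol article states: "Randomization will be stratified on the number of hospital visits concerning asthma in the past 6 months". There are four strata (0-1, 2-3, 4-5, 6 or more visits). The reason given is that "it is known that previous exacerbations and health care utilization are risk factors for future exacerbations". Allocation is by "stratified block randomization with multiple block sizes (2, 4, and 6) into either group A or group B with an allocation ratio of 1:1".

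Under Data and Statistical Analyses, "Univariate analyses will be performed with SPSS software". The primary outcomes, utilisation and costs, are compared by a t test or, if the data are not normal, a "nonparametric Mann-Whitney U test) will be used to compare the primary outcomes between eHealth care and standard care", at P≤.05. Neither the strata nor the prior visit count appears in that comparison.

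The Sample Size section uses the same unadjusted test: "A power simulation was performed for a Mann-Whitney-Wilcoxon 2-sided test". It gives each arm a single rate, apart from nonadherent children: "The health care utilization was assumed to be Poisson distributed with means according to the clinical feasibility study".

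**The concern.** Stratified blocks make the arms similar on prior visits. If prior visits predict the outcome, the difference between arms varies less from one randomisation to the next than in an unstratified trial. An unadjusted two-sample test does not know this: it counts the variation between strata as noise. Its P values are then too large on average, its true level falls below 5%, and a real effect is more easily missed.

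The protocol's own reason for stratifying is that the factor is prognostic, and the prior count must be known for every child in order to randomise. The analysis therefore sets aside information that the design has already collected and used. With 36 evaluable children, and an effect assumption taken from a feasibility study without a randomised control, lost precision matters most if the true reduction is smaller than planned.

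**Working it through.** **Inputs from the protocol article.** 18 per arm; two-sided test; "Together with the assumption of an Alpha Type 1 error of 0.05"; 3.9 and 0.7 outpatient consultations per half year; nonadherence 3 of 33; four strata; blocks of 2, 4 and 6.

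Rates per 3 months: 3.9/2 = 1.95 and 0.7/2 = 0.35, a ratio of 0.35/1.95 = 0.18. Nonadherence: 3/33 = 9.1%, at the control rate.

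**Step 1: the stated power.** Simulating Poisson 1.95 against 0.35 with 9.1% nonadherence and 18 per arm gives Mann-Whitney power of 97.1% with continuity correction and 97.3% without. The article states 97.1%, so it reproduces. This model contains no effect of prior visits.

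**Step 2: direction.** If the strata explain a share R² of outcome variance and the arms are perfectly balanced on them, the variance of the arm difference shrinks by the factor (1 − R²) while the unadjusted test uses the full variance. In large samples:

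level ≈ 2Φ(−1.96/√(1 − R²))

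- R² = 0.10: 1.96/0.949 = 2.07, level 3.9%
- R² = 0.36: 1.96/0.800 = 2.45, level 1.4%
- R² = 0.57: 1.96/0.656 = 2.99, level 0.3%

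Incomplete blocks leave some imbalance, so the real levels should lie somewhat higher.

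**Step 3: simulation by strength of the strata.** 6,000 trials per setting, N = 36, the plan's blocks, overall control mean 1.95. Assumed stratum shares are 40/30/20/10% for R² above 0, with assumed rate multipliers:

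- 0.8/1/1.3/1.5 (R² = 0.10)
- 0.5/1/1.6/2.2 (R² = 0.36)
- 0.5/2.5/4.5/7 (R² = 0.57, rate proportional to prior visits)

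For the last: the mean multiplier is 2.55 and the mean square is 10.925, so the relative variance is 10.925/2.55² − 1 = 0.680. Then R² = 1.95² × 0.680/(1.95² × 0.680 + 1.95) = 0.57.

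| R² | Level: Mann-Whitney / t / van Elteren | Power, planned effect: Mann-Whitney / van Elteren | Power, halved rate: Mann-Whitney / van Elteren |
|---|---|---|---|
| 0 | 5.0 / 5.0 / 5.2% | 96.9 / 96.6% | 53.4 / 52.7% |
| 0.10 | 4.2 / 4.4 / 5.3% | 96.4 / 96.1% | 49.3 / 50.2% |
| 0.36 | 2.1 / 2.3 / 5.4% | 92.4 / 93.9% | 37.2 / 48.0% |
| 0.57 | 0.7 / 0.9 / 5.1% | 79.2 / 90.4% | 17.5 / 42.6% |

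Monte Carlo error is about 0.3 points at the 5% level. With R² = 0.57 but unstratified randomisation the unadjusted levels are 4.4% (Mann-Whitney) and 4.6% (t). The conservatism therefore comes from stratifying and then not adjusting.

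**Step 4: simulation with child-level rates.** Each child has a gamma-distributed rate (shape k, mean 1.95 per 3 months) that drives both the prior 6-month count and the outcome. Both k and full persistence are assumed. Ranges are over repeated sets of runs.

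| k | Level: Mann-Whitney / van Elteren | Power, planned effect | Power, halved rate |
|---|---|---|---|
| 1 | 0.8-1.2 / 3.9-4.7% | 74-75 / 84% | 22-23 / 38-39% |
| 2 | 2.1-2.7 / 4.7-5.2% | 87-88 / 90-91% | 34-38 / 44-47% |
| 4 | 2.9-3.7 / 4.1-5.0% | 92 / 92% | 47-48 / 50-52% |

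The loss is about 0 points (k = 4) to 9 points (k = 1) at the planned effect, and about 4 to 17 points for a halved rate.

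**Step 5: partial persistence.** If half the children draw a fresh rate for the outcome period, the Mann-Whitney level is 3.1% (k = 1) and 4.2% (k = 2). Halved-rate power is then 23 against 27% and 36 against 38%, a loss of 4 and 2 points.

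**The case against.** The strongest reply is that the size cannot be read from the protocol. It gives no correlation between prior visits and the 3-month outcome, no between-child variance and no expected stratum distribution. Under its own planning model the unadjusted test runs at 5.0% and loses nothing. The stratifier counts hospital visits, the cited reason concerns exacerbations, and the primary outcomes are broader (all health care activities, and costs). The article itself notes the episodic nature of asthma, so full persistence is a favourable assumption for adjustment: it implies correlations of about 0.73, 0.57 and 0.40 for k = 1, 2 and 4. All of this stands, and it rules out several stronger readings that a reader might infer:

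- That the test certainly runs far below 5%. This holds only if the factor is strongly prognostic.
- That reported confidence intervals would be wrong. The article specifies none for this comparison.
- That prior visits are the strongest available predictor. The article does not rank predictors.
- That the low power at k = 1 is caused by ignoring the strata. Most of it comes from variation between children: van Elteren reaches only 38-39% there for a halved rate.
- That a positive result would be suspect. The error is conservative.

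Two replies do not dispose of the point. The planning model shows no loss only because it lets prior visits predict nothing, which does not fit the reason given for stratifying. And although a separate analysis plan may exist, the article itself names the test, threshold and software, so this is a stated choice. Univariate might mean only one outcome at a time, but the two named tests take no covariate in any case.

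**Conclusion.** The point holds as a conditional one. The design uses a factor that the protocol calls a risk factor, and the stated primary comparison leaves it out. The consequence is a conservative test and some loss of power. How much rests on assumed prognostic strength: little if the strata explain up to about 10% of the variance, material if they explain a third or more. At the planned effect the loss is modest in most settings. The largest, about 11 points (90.4 − 79.2), arises when rates are proportional to prior visits. The loss is greater if the true reduction is smaller than planned. The conclusion is confined to the primary comparison: the article does not name the test for the interim look, and no size is claimed there. It is a worthwhile correction, not a threat to validity.

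**What to change.** In Data and Statistical Analyses, make the primary comparison account for the stratification factor.

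- **Utilisation:** a van Elteren test stratified by the randomisation strata, or a dispersion-scaled Poisson model with arm and prior 6-month visit count. In the gamma model the latter, using log baseline visits, had 51, 54 and 56% power for a halved rate (k = 1, 2, 4), and the adjusted tests' type I error was 3.6-5.3%.
- **Costs:** the same stratified rank test, or a model suited to costs with the same covariate. A count model does not serve this outcome.
- **Sparse strata:** a merging rule set in advance. If 10% of children fall in the top stratum, it holds 0.10 × 36 = 3.6 on average.
- **Sensitivity analysis:** the unadjusted test as now stated.

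This needs no new data, only changed wording and slightly more analysis work. If prior visits turn out not to be prognostic, the power given up is about 0 to 2 points: for van Elteren in the first table, 96.9 − 96.6 = 0.3 at the planned effect and 53.4 − 52.7 = 0.7 for a halved rate. The largest loss seen in any set of runs was about 3 points.

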**Assessments**							
	Baseline variables (age, gender, BMI, *z* score, GINA^b^ medication step, allergic rhinitis, asthma-related medical history, and baseline spirometry, such as FEV1^c^ and FVC^d^	✓	✓				
	Medical utilization data Number of visits (planned/ emergency/hospital admissions), diagnostic tests, telephonic/internet consultations, total health care costs			✓		✓	
	Questionnaire evaluations: health literacy (HLS^e^), asthma control (C-ACT^f^), quality of life (PAQLQ^g^ and EQ-5D-Y), self-management (PAM-13^h^)		✓		✓		✓
	Quality of care (CSQ^i^)				✓		✓
	Monitoring data: medication use, sleep, nocturnal heart/respiratory rate, nocturnal coughing/ wheezing, air quality, lung function, and oxygen saturation			✓		✓	
	Intervention data: intervention use logs, and nebulizer use			✓(A^a^)			
	eHealth–specific evaluations: system usability (SUS^j^), technology acceptance (TAM^k^), and interview				✓(A^a^)		

^a^Depending on the randomization. Group A receives eHealth care, and group B receives standard care within the intervention period (t_1_).

^b^GINA: Global Initiative for Asthma.

^c^FEV1: forced expiratory volume.

^d^FVC: forced vital capacity.

^e^HLS: Health Literacy Survey.

^f^C-ACT: Childhood Asthma Control Test.

^g^PAQLQ: Pediatric Asthma Quality of Life Questionnaire.

^h^PAM-13: 13- Item Patient Activation Measure.

^i^CSQ: Client Satisfaction Questionnaire.

^j^SUS: System Usability Scale.

^k^TAM: Technology Acceptance Model.

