### Study Setting and Eligibility Criteria

A total of 40 children with moderate-to-severe pediatrician-diagnosed asthma between 4 and 11 years of age will be recruited from the Medisch Spectrum Twente (MST) hospital in Enschede, the Netherlands. Pediatrician-diagnosed asthma includes confirmation of asthma diagnosis with a positive reversibility or challenge test [2]. Children are classified as having moderate or severe asthma if they meet one of the criteria shown in Table 2. Children with comorbid chronic diseases, previous asthma eHealth care intervention trial experiences [34], or children/parents with an inability to understand or speak Dutch are not eligible to participate. Additionally, children that do not live for more than 80% at the same address or those who do not have a stable Wi-Fi connection at home are excluded from participation.

Participants will be recruited from the pediatric department of MST using consecutive sampling, which is expected to take 40 weeks. A study flyer will be displayed in the pediatric ward and distributed among pediatric patients with asthma after an outpatient visit. Patients who indicate that they may be contacted will be contacted after 1 week, but patients may also contact the researchers themselves for further verbal and written study information. Offline written informed consent from parents will be obtained prior to participation in this study.

**Table 2 table2:** Criteria for classification as moderate or severe asthma.

Condition	Moderate asthma	Severe asthma
Medication	GINA^a^ step 3/4 or uncontrolled (C-ACT^b^<20) in GINA step 2 [2]	Step 5 or uncontrolled (C-ACT<20) despite medium to high-dose ICS^c^-LABA^d^ in step 4
Recent exacerbation (<3 months) despite controller medication	Needing a salbutamol regimen of oral cortical steroid therapy	Leading to a hospital admission
Bronchial hyperreactivity assessed with an exercise challenge test in cold air [37,38]	Between 25% and 50% decrease in FEV1^e^ [39]	>50% decrease in FEV1 [39]

^a^GINA: Global Initiative for Asthma.

^b^C-ACT: Childhood Asthma Control Test.

^c^ICS: inhaled corticosteroid.

^d^LABA: long-acting beta2-agonist.

^c^FEV1: forced expiratory volume.

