### Outcome Measures

Demographic characteristics (age, gender, medication use, other medication use, allergy due to aeroallergens, eczema, doing sports, and smoking behavior at home) will be retrieved from electronic patient records.

The primary outcome variables are health care utilization and costs. All health care activities (ie, hospital admissions, outpatient visits, emergency visits, diagnostic activities, etc) will be labeled using the Dutch health care registration system of the Dutch Healthcare Authority. The accompanying health care costs will be calculated using activity-based costing [50]. Furthermore, the specific eHealth care costs will be calculated using bottom-up gross costing, consisting, for example, of the working hours of the HCPs and the depreciation costs of the monitoring devices [50].

Multimedia Appendix 1 contains the description and analysis of other outcome variables to investigate the effects of the eHealth intervention, which will enable research that can further improve pediatric eHealth asthma care.

All data will be handled according to the EU GDPR and the Dutch Act on the Implementation of the GDPR and securely stored in the Castor EDC system.

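### The only stated stopping criterion is a rise in health care utilization, an outcome that mixes visits the intervention should remove with emergency visits and admissions, so it does not measure harm

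*Protocol article*

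**What the plan says.** Data and Statistical Analyses sets the timing, "An interim analysis will be conducted after half the participants are done with the intervention", and then the rule: "In case the interim analysis reveals a significant increase in health care utilization in the intervention group, this study will be prematurely ended". No other criterion for ending the trial early is stated.

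The rule does not say which contacts make up utilization. Outcome Measures describes the primary outcome broadly: "All health care activities (ie, hospital admissions, outpatient visits, emergency visits, diagnostic activities, etc) will be labeled". Table 1 lists the utilization data as "Number of visits (planned/ emergency/hospital admissions), diagnostic tests, telephonic/internet consultations, total health care costs". The types are therefore recorded separately, but they all belong to one outcome.

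The Hypothesis section predicts that this outcome will fall. Sample Size puts the fall at 80% and supports it with one type of contact only: "average reduction in the number of outpatient consultations from 3.9 to 0.7 (SD 1.8) per patient per half year".

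**The concern.** The stopping criterion is the efficacy outcome with its sign reversed. The intervention replaces clinic contact with portal contact and, under Home Nebulizer Therapy, allows some acute treatment to start at home under video supervision. If this led to loss of control or late presentation, the signal would be more emergency visits and admissions; the Introduction itself links poor control to both. In a summed count, those events are set against a large planned fall in outpatient consultations. The interim could then pass, or even look favourable, while acute care rises.

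The opposite failure is also possible. Table 1 counts internet consultations, and the intervention works through such contacts. If they enter the count, the intervention arm could show a significant increase with no child worse off. In both cases the result of the rule says little about harm.

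**Working it through.** **Inputs from the protocol.** Outpatient consultations per half year are 3.9 before and 0.7 after, halved for 3 months: 3.9/2 = 1.95 (control) and 0.7/2 = 0.35 (intervention). Non-adherence is 3/33, at the control rate. The test is a two-sided Mann-Whitney test at 0.05, with 18 per arm for power. The interim is at half of 40 children, taken as 10 per arm.

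**Assumed inputs.** The protocol gives no rate of emergency visits plus admissions. Control rates of 0.1, 0.2, 0.3 and 0.5 per child per 3 months are assumed, with Poisson counts multiplied by 2, 3, 5 or 8 in the intervention arm.

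**Step 1: the protocol's own figures.** Simulating Poisson 1.95 against 0.35 with 3/33 non-adherence and 18 per arm gives power of 97.2% with continuity correction and 97.5% without. The stated figure is 97.1%. Follow-up power, reading the lasting effect as 80% of the difference, is 81.5% against the stated 80%. The model therefore matches the one behind the sample size.

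**Step 2: break-even.** The expected outpatient fall is 1.95 − 0.35 = 1.60 per child. After non-adherence it is 1.60 × (1 − 3/33) = 1.45. Acute events would have to rise by about 1.45 per child in 3 months before the two arms' mean totals were equal.

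**Step 3: the rule on outpatient plus acute contacts** (10 per arm, 5,000 simulated trials per scenario). Each cell gives the percentage of trials with a significant increase, then the percentage with a significant decrease, in the intervention arm.

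| Rise in acute events | Control rate 0.1 | 0.2 | 0.3 | 0.5 |
|---|---|---|---|---|
| Doubling | 0 / 68 | 0 / 55 | 0 / 45 | 0.04 / 28 |
| Tripling | 0 / 59 | 0 / 40 | 0.1 / 25 | 0.4 / 9 |
| Fivefold | 0 / 41 | 0.04 / 16 | 0.8 / 5 | 8.7 / 0.3 |
| Eightfold | 0.04 / 23 | 1.9 / 2.7 | 11 / 0.3 | 59 / 0 |

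A t test, which the protocol also allows, gives nearly the same results.

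**Step 4: the same test on acute events alone.** Percentage of trials with a significant increase:

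| Rise in acute events | Control rate 0.1 | 0.2 | 0.3 | 0.5 |
|---|---|---|---|---|
| Doubling | 4 | 9 | 13 | 21 |
| Tripling | 10 | 23 | 34 | 54 |
| Fivefold | 30 | 59 | 76 | 94 |

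Repeat simulations moved these values by about one percentage point (for example 3 to 21% for a doubling and 11 to 55% for a tripling).

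**Step 5: counting portal contacts.** Add an assumed 4 internet consultations per intervention child in 3 months to the model of Step 3, with no rise in acute events from a control rate of 0.2. The rule then fires in about 80% of trials. The protocol gives no expected number of such contacts, so this shows the direction of the effect and does not estimate it.

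**The case against.** **The rule does not say total.** This is correct. The pooled reading comes from Outcome Measures and Table 1, and a component-by-component interim would also fit the words. That does not rescue the criterion. It would still not say which component counts, and the only component given a rate in the protocol is outpatient consultations.

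**The direction of the failure depends on the counting rule.** This also stands. Leaving out portal contacts masks harm; including them can make the rule fire without harm. Diagnostic tests are not in the simulation either. If each acute event brought further counted activities, the rule would fire more often.

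**The acute rates are assumed, and large rises do trigger the rule.** At a control rate of 0.5 it fires in 59% of trials at eightfold and about 76% at ninefold. A reader might infer that the rule can never fire. The figures do not support that.

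**Other safeguards exist.** A reader might infer that this is the trial's only protection. The protocol does not support that either. The care pathway includes weekly multidisciplinary review of data trends, replies within one workday, an instruction to go straight to emergency care, and the option of a hospital visit at any time. Home nebulizing is supervised and has starting criteria. Staff are unblinded. Adverse event reporting may be set out in the full protocol, which this article condenses. The rule is also not labelled a safety rule. What remains is narrower: the one criterion stated for ending the trial measures the wrong quantity.

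**Conclusion.** The point holds for the stopping criterion as stated. If outpatient and acute contacts are summed, a two- to fivefold rise in acute events is largely offset by the planned outpatient fall. The rule fires in at most about 0.4% of trials at tripling and in 0 to 9% at fivefold, across assumed control rates of 0.1 to 0.5. At tripling, the same test shows a significant decrease in utilization in 9 to 59% of trials, so the interim can look like benefit while acute care rises. Only very large rises at high base rates trigger it. If portal contacts are counted, the criterion can fire on planned delivery of the intervention.

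These sizes rest on 10 children per arm, Poisson counts, the protocol's own outpatient rates and the assumed acute rates. The qualitative conclusion needs only that the criterion mixes contacts the intervention is meant to change with contacts that would signal harm. No claim is made that other safety oversight is absent.

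**What to change.** In Data and Statistical Analyses, base the interim harm comparison on asthma emergency visits plus hospital admissions, counted separately from planned visits and from telephone or internet consultations, using the Table 1 categories. Give the counts by arm to those reviewing the interim. Report overall utilization at that point descriptively only. The threshold for ending the trial is for the sponsor and ethics committee to set.

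The cost is about one sentence in the protocol and no new data, since Table 1 already separates the contact types. The limitation is sensitivity. With 10 per arm, the acute-only test detects a doubling in about 3 to 21% of trials and a tripling in about 11 to 55%. A P ≤ .05 test should therefore not be the only trigger; the counts themselves must be reviewed.
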